### Outcomes

The primary outcome is the change in insulin sensitivity, assessed using the homeostatic model assessment for insulin resistance (HOMA-IR), derived from fasting glucose and insulin concentrations. The secondary outcome is the change in gut microbiota composition and diversity, analyzed through 16S rRNA gene sequencing. Alpha and beta diversity indexes will be calculated to evaluate within- and between-sample diversity, and differential abundance analysis will be performed to identify microbial taxa associated with each intervention.

### Sample Size

The sample size for this crossover trial was estimated based on detecting a medium effect size (Cohen *f*=0.25), consistent with findings from a recent meta-analysis of soluble fiber supplementation in T2DM, which reported moderate standardized mean differences for HOMA-IR (standardized mean difference −0.58, 95% CI −0.86 to −0.29) [23]. Using G*Power 3.1.9.6, we computed the required sample size for a within-subject repeated-measures ANOVA with 3 conditions (sucralose, saccharin, and placebo), assuming α=.05, and statistical power at 80%, and a moderate correlation (*r*= 0.5) among repeated measurements [24]. The analysis indicated that a minimum of 28 participants would be required. To account for potential dropout or noncompliance, we will recruit 33 participants.

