### Statistical Analysis

Clinical data will be presented as mean (SD) unless stated otherwise. Statistical analyses will be performed using SPSS Statistics (version 28.0; IBM Corp) [40]. The normality of continuous variables will be assessed using the Shapiro-Wilk test. Participants’ baseline characteristics will be summarized using descriptive statistics. Differences in glycemic responses across the 3 study arms will be assessed using either 1-way ANOVA or the Kruskal-Wallis test, depending on data distribution. Changes in clinical variables before and after the intervention will be analyzed using repeated-measures ANOVA, with time (before vs after), group (intervention arm), and the time-by-group interaction as factors. Sociodemographic characteristics, dietary intake, and physical activity levels will be considered as covariates where appropriate. A *P* value of <.05 will be considered statistically significant. Analyses will be conducted according to the intention-to-treat principle, with per-protocol analyses performed for participants who complete the study without major deviations. Missing data will be handled using appropriate imputation methods, and any exploratory analyses will be clearly identified and interpreted with caution.

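### The 80% power at 28 participants is computed for three measurements correlated at 0.5, while the primary outcome is a pre-to-post change over six visits; for that change the plan supports only a range of power.

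*Protocol article*

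**What the plan says.** The Sample Size section of the protocol article bases the trial on "detecting a medium effect size (Cohen *f*=0.25"). It supports this with a meta-analysis of soluble fibre in type 2 diabetes, "which reported moderate standardized mean differences for HOMA-IR (standardized mean difference −0.58, 95% CI −0.86 to −0.29"). On the model it states that "we computed the required sample size for a within-subject repeated-measures ANOVA with 3 conditions (sucralose, saccharin, and placebo"), "assuming α=.05, and statistical power at 80"%, with a correlation of 0.5 among the repeated measurements. The result: "The analysis indicated that a minimum of 28 participants would be required". Recruitment is set at 33 to allow for dropout or noncompliance.

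The Outcomes section reads: "The primary outcome is the change in insulin sensitivity, assessed using the homeostatic model assessment for insulin resistance (HOMA-IR"). Study Design and Table 1 provide six visits with blood sampling, one before and one after each of the three interventions. The Statistical Analysis section says: "Changes in clinical variables before and after the intervention will be analyzed using repeated-measures ANOVA, with time (before vs after), group (intervention arm") and their interaction as factors. An earlier sentence in that section also plans a comparison of glycemic responses across the three arms.

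**The concern.** The power model has three measurements per participant; the outcome and its planned test use six. This matters because the calculation halves the error variance on the strength of the 0.5 correlation between conditions. Taking each phase's change from its own baseline already removes the participant's stable level, so that gain cannot simply be counted again. Differencing also adds the noise of a second measurement. Whether the two effects cancel depends on correlations that the article does not give.

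At stake is how a null result would be read. The Discussion expects the findings to inform dietary recommendations and policy on sweeteners. A non-significant HOMA-IR comparison from a trial described as having 80% power would look more reassuring than it should if power for the change is materially lower.

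**Working it through.** **Inputs.** From Sample Size: f = 0.25, α = .05, m = 3 conditions, r = 0.5, N = 28 (33 recruited). From Study Design and Outcomes: a pre and a post value in each of three phases, with the change as primary outcome. Not given: the pre-post correlation within a phase, the SD of the change, and the SD that scales f.

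**Step 1: reproduce the plan.** For a one-group within-subject ANOVA with sphericity, λ = N·m·f²/(1−r), with df = 2 and 2(N−1).
- N = 27: λ = 27·3·0.0625/0.5 = 10.125, power 79.6%.
- N = 28: λ = 28·3·0.0625/0.5 = 10.5, power 81.2%.
- N = 33: λ = 33·3·0.0625/0.5 = 12.375, power 87.8%.

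The minimum is 28, as stated.

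**Step 2: the change, with r = 0.5 among all six values.** Let σ² be the variance of a single value, r_w the pre-post correlation within a phase, and let all cross-phase correlations be equal.
- Variance of a change = 2(1−r_w)σ². At r_w = 0.5 this is 1.0σ².
- Covariance between changes from two phases = (post-post) − (post-pre) − (pre-post) + (pre-pre) = 0.
- λ = N·3·f²/[2(1−r_w)]. At N = 28 this is 28·3·0.0625/1.0 = 5.25, power 50.1%. At N = 33 it is 6.1875, power 57.7%.

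A simulation of 20,000 trials per sample size gave 50.3% and 58.2%. In this scenario 80% power needs 53 completers.

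**Step 3: vary the within-phase correlation** (f in single-value SD units, equal cross-phase correlations).

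| r_w | Power at 28 | Power at 33 |
|---|---|---|
| 0.4 | 43% | 50% |
| 0.5 | 50% | 58% |
| 0.6 | 60% | 68% |
| 0.7 | 73% | 81% |
| 0.75 | 81% | 88% |
| 0.8 | 89% | 94% |

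**Step 4: read f and r as describing the three change scores.** With f in change-SD units and a correlation r_c between changes from different phases, λ = N·3·f²/(1−r_c).
- r_c = 0: 50% at 28.
- r_c = 0.2: 60% at 28.
- r_c = 0.4: 73% at 28.
- r_c = 0.5: λ = 10.5, so 81.2% at 28 and 87.8% at 33, the plan's own figures.

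**The case against.** The strongest reply is that the Sample Size section never says its three measurements are single HOMA-IR values. Read as three change scores correlated at 0.5, the same inputs make 28 exactly right. The planned comparison of glycemic responses across three arms also fits a three-level model. The SD behind the cited standardized mean difference is not visible, and a condensed article may leave such detail to the full protocol.

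Much of this stands. A reader might infer that the trial's true power is 50% to 58%, or that the 28 was miscalculated. The documents support neither. Extending 0.5 to all six values is an assumption: two values about a week apart may well correlate more strongly than values from phases separated by a 4-week washout. At 33 completers, a within-phase correlation of 0.7 already gives 81%. Nor does moving f to the change-SD scale settle the matter, because the result there depends on the correlation between changes.

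The reply does not rescue the 80% as published. The ordinary meaning of a correlation among repeated measurements is one among the measured values. The change-score reading needs separate support: half the variance of a 7-day change would have to be a participant-specific shift that recurs under sucralose, saccharin and placebo. Equal correlation among the values implies zero correlation between those changes. The Discussion's limitation about a modest sample size gives no power figure.

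**Conclusion.** The concern holds as a mismatch between the power model and the declared primary outcome. The 28 is arithmetically correct for the model entered.

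For the pre-to-post change, 80% power at 28 requires one of two things: a within-phase pre-post correlation of about 0.75 or more (f in single-value SD units, equal cross-phase correlations), or a correlation of about 0.5 between 7-day changes under different products (f in change-SD units). The article states and justifies neither. If r = 0.5 applies equally among all HOMA-IR values, power is about 50% at 28 and 58% at 33. That is one scenario. Over within-phase correlations of 0.4 to 0.8 the range is 43% to 89% at 28 and 50% to 94% at 33. All figures assume sphericity and complete data at the stated number.

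**What to change.** Keep 33 participants. In Sample Size:
- State whether f = 0.25 and r = 0.5 refer to HOMA-IR values or to changes, and which SD scales f.
- Replace the single 80% claim with power for the time-by-group (change) test at 28 and 33 over a stated range of correlations. Include the 50%/58% case as one scenario. Alternatively, keep 80% and justify the correlation it needs.
- Carry the resulting range into the limitations paragraph of the Discussion.

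The cost is one recalculation and some rewording, with no added participants or procedures. No participant had been enrolled as of December 2025. The downside is that the stated power may look less favourable.

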## Methods

### Study Design

This study is a double-blind, randomized, placebo-controlled crossover trial. The crossover design allows each participant to serve as their own control across 3 intervention phases. Each participant will complete a 12-week protocol comprising a 1-week run-in period followed by 3 intervention phases, each separated by a 4-week washout period. A total of 6 study visits, comprising 3 preintervention and 3 postintervention assessments, will capture baseline and postintervention data. During the run-in and washout periods, participants will maintain their habitual diet and physical activity. The study will be conducted at a government primary care facility situated in an urban area. Recruitment will be facilitated through clinic listings and physician referrals. Written informed consent will be obtained after participants receive detailed verbal and written explanations of the study procedures, risks, and rights. The study timeline is summarized in Figure 1.

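### The 80% power behind the 28 participants is calculated for one value per condition and is not shown for the primary outcome, a pre-to-post change in HOMA-IR in each phase

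*Protocol article*

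**What the plan says.** Four sections of the protocol article bear on this.

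- **Sample Size.** The target is "detecting a medium effect size (Cohen *f*=0.25" (Cohen's f), and the test is a "within-subject repeated-measures ANOVA with 3 conditions (sucralose, saccharin, and placebo", which means one value per condition. The remaining inputs are given as "assuming α=.05, and statistical power at 80%, and a moderate correlation (*r*= 0.5) among repeated measurements". The result is "The analysis indicated that a minimum of 28 participants would be required", followed by "To account for potential dropout or noncompliance, we will recruit 33 participants". The section does not mention the pre-phase values, the variance of a change or the correlation between changes.
- **Outcomes.** "The primary outcome is the change in insulin sensitivity, assessed using the homeostatic model assessment for insulin resistance (HOMA-IR". The index is computed from a fasting blood sample.
- **Study Design.** "A total of 6 study visits, comprising 3 preintervention and 3 postintervention assessments, will capture baseline and postintervention data". Table 1 confirms a blood sample at each of these six visits.
- **Statistical Analysis.** "Changes in clinical variables before and after the intervention will be analyzed using repeated-measures ANOVA". The factors are time, intervention arm and their interaction. A separate sentence assigns one-way ANOVA or Kruskal-Wallis to differences in glycemic response across arms. The section does not say which of the two is the primary test for HOMA-IR.

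**The concern.** The calculation uses three numbers per participant; the declared outcome uses six. Subtracting a baseline removes variation that the baseline and post values share, but adds the baseline's own measurement noise. In a crossover the participant already serves as their own control, so a good part of the shared variation is gone before any baseline is subtracted. Unless the pre and post values within a phase agree clearly better than values from different phases, subtraction costs power.

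The 80% claim is therefore attached to a different quantity from the primary outcome. A null result for the change could be read as reassurance about sweeteners in type 2 diabetes, and the Discussion expects the findings to inform dietary recommendations and policy. The test might have had little better than an even chance of detecting the effect it was planned for. No participants had been enrolled as of December 2025, so this can be settled before there are data.

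**Working it through.** **Inputs from the Sample Size section:** f=0.25, m=3 conditions, r=0.5, alpha=0.05, n=28 (33 recruited). Sphericity is assumed throughout. Power comes from the noncentral F distribution with df1=m-1=2 and df2=(n-1)(m-1).

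**Step 1: the plan's own figure.** For one value per condition,

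lambda = n × m × f² / (1 - r).

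- n=27: 27 × 3 × 0.0625 / 0.5 = 10.125, power 79.6%.
- n=28: 28 × 3 × 0.0625 / 0.5 = 10.5, power 81.2%.

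So 28 is the smallest n that reaches 80%. The arithmetic is right for that test.

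**Step 2: the change, with r=0.5 among all six measurements.** In units of the raw variance:

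- Variance of one change = 2(1 - r) = 2 × 0.5 = 1, so the SD of change equals the raw SD, and it does not matter which of the two f is scaled by.
- Covariance of changes from two phases = r + r - r - r = 0, so the changes are uncorrelated.

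Hence lambda = n × m × f² / [2(1 - r)] = n × m × f², half the value in Step 1.

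- n=28: 28 × 3 × 0.0625 = 5.25, power 50.1%.
- n=33: 33 × 3 × 0.0625 = 6.19, power 57.7%.
- 80% is first reached at n=53 (lambda 9.94, power 80.1%).

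Simulation with 10,000 trials per sample size gave 49.8% at n=28, 57.6% at n=33 and 80.3% at n=53 for the change, and 81.8% at n=28 for the single post value.

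**Step 3: higher correlation within a phase.** This is an assumption; the article gives no such figure. Let rw be the pre-post correlation within a phase, with the between-phase correlation rb held at 0.5 and f on the raw SD.

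- Change: lambda = n × m × f² / [2(1 - rw)].
- Covariate adjustment: the difference between two post values has variance 2(1 - rb) - [2(rw - rb)]² / [2(1 - rb)]. At rb=0.5 this is 1 - 4(rw - 0.5)². Lambda is n × m × f² divided by half that variance.

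| rw | lambda, change | power, change, n=28 | lambda, covariate | power, covariate, n=28 |
|---|---|---|---|---|
| 0.5 | 5.25 | 50% | 10.5 | 81% |
| 0.6 | 6.56 | 60% | 10.94 | 83% |
| 0.7 | 8.75 | 73% | 12.5 | 88% |
| 0.8 | 13.1 | 89% | 16.4 | 95% |

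At rw=0.75 the change has lambda 5.25 / 0.5 = 10.5, the same as in Step 1, so power is 81%. The covariate figures take the slope to be the within-participant one and ignore the single degree of freedom spent on it.

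**Step 4: f and r read as properties of the changes.** With rc the correlation between changes from different phases, lambda = n × m × f² / (1 - rc). At n=28:

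| rc | lambda | power |
|---|---|---|
| 0 | 5.25 | 50% |
| 0.1 | 5.83 | 55% |
| 0.2 | 6.56 | 60% |
| 0.3 | 7.5 | 66% |
| 0.5 | 10.5 | 81% |

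If all between-phase correlations are equal, rc is zero whatever rw is, because the four covariance terms cancel as in Step 2.

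**The case against.** The strongest reply is that the three values entered could themselves be the changes. Then r=0.5 is the correlation between changes, and 28 gives 81% as stated. The wording does not exclude this. Nor do the documents give the correlation between changes; zero follows only from assuming equal between-phase correlations.

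Secondly, 50% is the low end of the range. It supposes that values about a week apart agree no better than values separated by a four-week washout. A within-phase correlation of 0.75 restores 81% at n=28, and 0.7 is enough if all 33 complete (lambda 6.19 / 0.6 = 10.3, power 81%).

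Thirdly, the Statistical Analysis section does not clearly make the time-by-arm interaction the sole primary test.

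All three stand as limits on the claim. A reader might infer that the trial has 50% power rather than 80%, or that 28 is a miscalculation. The documents support neither: 28 is correct for the test described, and 50% depends on applying r=0.5 to all six raw values.

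The mismatch itself remains. Each phase has its own baseline, so no shared baseline makes the changes correlate, and 0.5 between them would need a justification that the article does not offer. Nor does it state a within-phase correlation of 0.75.

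**Conclusion.** The point holds in limited form: the stated 80% belongs to a comparison of one value per condition and is not shown for the change in HOMA-IR that the article names as primary. Under r=0.5 among all six measurements, power for the change is about 50% with 28 completers and 58% with 33. Over the other correlations examined, power at n=28 runs from 50% to 89%. It reaches 80% only at a within-phase correlation of about 0.75 or more (between-phase 0.5, f on the raw SD), or at a correlation of about 0.5 between changes. These figures take f=0.25 as given and treat the time-by-arm interaction as the test of the change. They describe power under stated assumptions and do not predict how HOMA-IR will behave in these patients.

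**What to change.** Make post-phase HOMA-IR the primary dependent variable in a within-participant mixed model, with pre-phase HOMA-IR as a covariate and not a subtracted baseline. Specify the covariate so that its slope is estimated within participants, for example by also including each participant's mean pre-phase value. Name the comparison of arms in that model as the primary test. This keeps about 81% at n=28 under the plan's own r=0.5, and gains if the within-phase correlation is higher. A log scale for HOMA-IR is optional and not part of this point.

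If the change score or the interaction is kept as primary, state whether f and r refer to single values or to changes, and report power for that contrast over the range of correlations shown above.

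The cost is an amendment to the wording of the Outcomes, Sample Size and Statistical Analysis sections, and possibly to the registration and the ethics documents. The first option needs no extra participants, visits or samples.

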### Ethical Considerations

This study was approved by the Universiti Kebangsaan Malaysia Research Ethics Committee (UKM/PPI/111/8/JEP-2025-322) on July 15, 2025. Procedures follow the Declaration of Helsinki and institutional ethics standards. This study is registered with ClinicalTrials.gov (NCT07124585), first released on August 8, 2025.

Written informed consent will be obtained from all participants before enrolment. Participants will receive a verbal explanation of the study and will be given adequate time to review the participant information sheet. An optional separate consent form will be provided for the storage and future use of deidentified biospecimens in ancillary studies.

Participant privacy and confidentiality will be protected throughout the study. Identifiable information will be collected only as necessary and will be stored separately from research data using unique participant codes. All datasets will be deidentified before analysis, and access to identifiable information will be restricted to authorized study personnel. No identifiable data or images will appear in publications or presentations.

Participants will receive financial compensation for time and transportation. Compensation for harm is not anticipated, as the interventions involve commercially available NNSs administered at doses considered safe. Any adverse events will be documented and managed according to institutional procedures, and medical care will be provided as needed.

### Data Collection

Data and biospecimens will be collected at baseline and after each intervention phase by trained research personnel as outlined in the study visit overview (Table 1).

**Table 1 table1:** Overview of data and biospecimen collection by study visit.

		Screening	Intervention 1		Intervention 2		Intervention 3	
			Visit 1	Visit 2	Visit 3	Visit 4	Visit 5	Visit 6
**Anthropometry**								
	Weight	✓	✓	✓	✓	✓	✓	✓
	Height	✓						
	Waist circumference		✓		✓		✓	
	Body composition		✓	✓	✓	✓	✓	✓
	Blood pressure		✓	✓	✓	✓	✓	✓
**Biological specimens**								
	Blood		✓	✓	✓	✓	✓	✓
	Stool		✓	✓	✓	✓	✓	✓
**Questionnaire**								
	Sociodemographic and medical history	✓						
	Medication record	✓	✓		✓		✓	
	Dietary record	✓	✓	✓	✓	✓	✓	✓
	Physical activity record	✓	✓	✓	✓	✓	✓	✓
	Test product compliance record			✓		✓		✓
	Adverse effect reports			✓		✓		✓

Anthropometric measurements will be obtained using standardized procedures. Body weight will be measured using a calibrated digital scale with participants wearing light clothing, while height will be measured using a stadiometer, ensuring an upright posture and proper head alignment. The average of 2 readings will be recorded for both weight and height, and BMI will be calculated as weight in kilograms divided by height in meters squared (kg/m²). Waist circumference will be measured at the midpoint between the lowest rib and the iliac crest using a nonstretchable measuring tape [25]. Body composition, including body fat and muscle mass, will be assessed using bioelectrical impedance analysis following standard premeasurement guidelines [26]. Blood pressure will be measured twice after a 5-minute rest using an automated sphygmomanometer, and the mean of both readings will be recorded.

For biological specimens, blood samples of approximately 15 mL will be collected from participants at each study visit by trained nurses after a 30-minute rest period. Analyses will include fasting glucose, fasting insulin, glycated hemoglobin (HbA_1c_), lipid profile, and kidney function indicators. Insulin resistance will be estimated using the HOMA-IR, derived from fasting glucose and insulin levels [27]. Samples will be transported and processed according to biosafety and quality control procedures to ensure sample integrity for biochemical analysis and future molecular investigations. Stool samples of approximately 1 g will be collected using standardized fecal collection tubes provided to participants. Preintervention samples will be collected a day before each intervention phase, and postintervention samples will be obtained immediately after the final intervention day. Participants will receive detailed written and verbal instructions to ensure correct collection and handling procedures [28].

Sociodemographic and medical history information will be obtained through structured interviews and verified against medical records. Medication use will be reviewed at each study visit. Dietary intake will be assessed using 3-day food records covering 2 weekdays and 1 weekend day. Investigators will review the records during face-to-face sessions using visual aids to ensure completeness and improve portion-size estimation accuracy. Nutrient intake will be analyzed using the Malaysian Food Composition Database [29]. Physical activity will be assessed using the short-form International Physical Activity Questionnaire, available in both English and Malay, which has been validated for the Malaysian population [30,31]. Test product compliance records and adverse event reports will be obtained during each postintervention visit. Any serious adverse event or major complaint will be promptly managed by the study physician and reported to the responsible authorities within 48 hours, with appropriate medical action documented. Leftover blood and stool biospecimens from each visit will be stored at −80 °C in the institutional biobank for future research on disease biomarkers, gene expression, or microbial function, subject to ethics approval and participant consent.

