### Intervention

Participants will receive 1 of 3 interventions: sucralose, saccharin, or a placebo, for 7 consecutive days during each intervention phase. Participants will consume the assigned capsule each morning after breakfast with plain water to standardize timing and minimize missed doses. Dosages will be adjusted based on body weight according to national guidelines, with 5 mg/kg for sucralose and 2 mg/kg for saccharin [22]. The placebo, consisting of 500 mg of calcium carbonate, will be administered under identical conditions and is considered physiologically inert at this dose [9].

Randomization and allocation concealment will be conducted by external personnel not involved in recruitment, data collection, or analysis. A computer-generated block randomization sequence will assign participants to 1 of 3 intervention orders (sucralose, saccharin, or placebo) to ensure balanced allocation across participants. All test products will be encapsulated in identical opaque capsules and packaged in indistinguishable small plastic pouches. Labeling will be performed by external personnel according to the intervention sequence, where each package will be marked as “first intervention,” “second intervention,” or “third intervention” to maintain blinding. Both participants and investigators will remain blinded throughout the data collection period. The randomization code will be securely stored and accessible only in the event of a medical emergency.

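### Scheduled adverse event reports skip Visits 3 and 5, so non-serious washout events are first asked about after a week on the next product

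*Protocol article*

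**What the plan says.** Under Methods, Data Collection, the article fixes when safety reports are taken: "adverse event reports will be obtained during each postintervention visit". Table 1 has a row labelled "Adverse effect reports" with ticks at Visits 2, 4 and 6 and none at Visits 1, 3 and 5. Text and table agree.

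Study Design describes "A total of 6 study visits, comprising 3 preintervention and 3 postintervention assessments", within a "12-week protocol comprising a 1-week run-in period followed by 3 intervention phases, each separated by a 4-week washout period". Under Intervention, each product is taken "for 7 consecutive days during each intervention phase". Visits 3 and 5 are therefore the pre-intervention visits that end the first and second washouts. Table 1 schedules blood, stool, dietary, physical activity and medication records at both.

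Three other statements on safety are not tied to a visit:

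- Data Collection: "Any serious adverse event or major complaint will be promptly managed by the study physician and reported to the responsible authorities within 48 hours".
- Participants: the study physician monitors and manages adverse events under institutional protocols.
- Ethical Considerations: any adverse event will be documented and managed under institutional procedures.

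**The concern.** In a crossover, an adverse event is informative about a product only if it can be placed in the right period. The clean moment to ask about a washout event is at the end of that washout, before the next product is started. Participants attend a visit at that moment, but no adverse event report is scheduled there. The question next comes when they have already taken another product for a week.

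Two things are at stake. First, attribution: a single recall window covers a long off-product stretch and a new exposure, so a mild event early in the washout may be forgotten, misdated or confused with the new product. Second, the baseline: Visits 3 and 5 supply the fasting blood and stool against which the next phase is judged. The protocol treats acute illness as an exclusion at entry and the need for antibiotics as a reason for withdrawal, so it already regards intercurrent illness as relevant. An untreated illness in the washout may not be known when that baseline is taken.

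**Working it through.** **Inputs** (protocol article)

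- Run-in: 1 week = 7 days (Study Design)
- Intervention phases: 3, of 7 days each (Study Design; Intervention)
- Washouts: 4 weeks = 28 days, between phases, so 2 of them (Study Design)
- Stated total: 12 weeks (Study Design)
- Scheduled adverse event reports: Visits 2, 4 and 6 (Data Collection; Table 1)

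**Step 1. Reproduce the stated duration.** 7 + 3 × 7 + 2 × 28 = 84 days; 84 / 7 = 12 weeks. This matches the article.

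**Step 2. Lay out the calendar**, counting the first run-in day as day 1.

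| Segment | Days | Scheduled adverse event report at its end |
|---|---|---|
| Run-in | 1–7 | none |
| Product 1 | 8–14 | Visit 2 |
| Washout 1 | 15–42 | none (Visit 3 is attended) |
| Product 2 | 43–49 | Visit 4 |
| Washout 2 | 50–77 | none (Visit 5 is attended) |
| Product 3 | 78–84 | Visit 6 |

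The article gives no calendar day for the visits. I assume each post-intervention visit falls at the end of its dosing week, about days 14, 49 and 84. If all three fall a day later, the spacing below does not change.

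**Step 3. Interval between scheduled reports.** 49 − 14 = 35 days and 84 − 49 = 35 days. Each interval is 28 washout days followed by 7 days on the next product.

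**Step 4. Example.** An event starting on day 16, two days after the last dose of product 1, is first asked about on about day 49. That is 49 − 16 = 33 days later, with product 2 taken on days 43–49.

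**Step 5. Share of time in washout.** First to last dose is 84 − 8 + 1 = 77 days. The washouts take 2 × 28 = 56 days; 56 / 77 = 0.727, or 73%.

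**Step 6. Effect of adding Visits 3 and 5.** The 35-day window splits into one of about 28 days, wholly in washout, and one of 7 days, wholly on product. Neither mixes the two.

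**The case against.** The strongest reply is that Table 1 fixes when a form is filled in, not when events may be noticed. Much of that stands:

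- Serious events and major complaints have the 48-hour route at any time. General monitoring and documentation are promised without a visit limit.
- Medication is reviewed at Visits 3 and 5 (Table 1 ticks both, and the text says every visit), so a treated washout illness can come to light before the next product. The need for antibiotics is already a ground for withdrawal.
- Every exposure week is followed by a report before the next exposure, so on-product events are asked about promptly.
- Safety is not among the stated outcomes, and the Statistical Analysis section describes no adverse event analysis by product.

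A reader might infer that washout events go unrecorded, or are counted against the wrong product. The documents do not support either reading. The first ignores the routes above. The second assumes that the forms at Visits 4 and 6 carry no onset date; the article does not describe the form, and an article commonly leaves that to the full protocol or case report form. With an onset date, an event first reported at Visit 4 can still be placed in the washout.

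What the reply does not remove is the schedule itself. The statements on general monitoring and documentation set no collection point, and the only statement that does leaves out Visits 3 and 5. Medication review does not reveal an event that was not treated.

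**Conclusion.** The point holds in a limited form. Non-serious washout events that are neither volunteered nor revealed by medication review are first solicited at Visit 4 or 6, after 7 days of the next product, with up to 35 days of recall across washout and new exposure. This weakens attribution and may leave untreated illness unknown at the next baseline. It is a schedule that the article states in both text and table, not a detail left out by condensation.

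The 73% describes time in washout. It should not be read as a proportion of events missed or misattributed, which the documents give no means to estimate. No sample size or stated primary or secondary analysis depends on the point, so it is a worthwhile refinement rather than a defect that threatens the trial.

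The conclusion assumes that post-intervention visits fall at about the end of each dosing week and that washouts last the stated 4 weeks.

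**What to change.** In Table 1, add the adverse event report at Visits 3 and 5. In the Data Collection text, say that it is taken at these pre-intervention visits as well as at each post-intervention visit, before the next product is started. State that onset dates are recorded, so that a washout event is placed in the washout following the preceding product and reported separately from on-product events. This also gives the general promises of monitoring and documentation under Participants and Ethical Considerations a collection point in the washouts.

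The cost is close to nil: the same form at two visits that participants already attend, two more ticks in the table and an edited sentence. The article reports no enrolment as of December 2025 and recruitment planned from January 2026. If recruitment has not begun, the change can apply to every participant.
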